#### Follow-up

Recruited patients will be sent a further questionnaire 3 months after recruitment. In order to improve response rates [60], initial non-responders will be sent a further reminder and questionnaire 2 weeks later. If they still do not respond they will be contacted by telephone 4 weeks after the initial questionnaire was sent and invited to either return the questionnaire by post or to complete it over the phone. An unconditional £5 gift voucher will be sent with each questionnaire as a token of appreciation or "thank you" [60].

Participants will be sent a further questionnaire 12 months after recruitment. Shortly afterwards, patients will be invited, either by the research team or the participating practices directly, to attend a follow-up appointment at their practice at a mutually convenient time/date. The location of these appointments will depend on staff and participating practices' availability and resources.

A £10 voucher redeemable at larger shops will be given to patients at the time of this visit in recognition of any travel expenses incurred and the time dedicated to attend the appointment. The researchers and practice staff (if appropriate) will be fully trained in the use of the devices for measuring cholesterol/HDL, cotinine and blood pressure. The results will be fed back to both clinicians and patients.

Patients will also be asked to consent to having their GP medical records checked for cholesterol, blood pressure, height and weight, duration of the index consultation, number of other consultations about health behaviours in the past year (since entering study) and relevant medications prescribed (e.g. nicotine replacement therapy or alternatives such as Bupropion or varenicline for smoking cessation, orlistat/sibutramine (sibutramine was available during the early part of the study, but was discontinued from availability in UK in January 2010) for weight loss, alcohol reduction treatment etc). The study team and the participating practices (if appropriate) will be responsible for research-related follow up.

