**Methods/Design:**

This cluster randomised controlled efficacy trial (RCT) will evaluate the outcomes and costs of this training intervention for General Practitioners (GPs) and nurses. Training methods will include: a practice-based seminar, online self-directed learning, and reflecting on video recorded and simulated consultations. The intervention will be evaluated in 29 practices in Wales, UK; two clinicians will take part (one GP and one nurse) from each practice. In intervention practices both clinicians will receive training. The aim is to recruit 2000 patients into the study with an expected 30% drop out. The primary outcome will be the proportion of patients making changes in one or more of the four behaviours at three months. Results will be compared for patients seeing clinicians trained in BCC with patients seeing non-BCC trained clinicians. Economic and process evaluations will also be conducted.

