## Methods/Design

### Study Design

This study is a cluster randomised controlled trial with randomisation at the level of practice. Behavioural outcomes will be assessed for eligible patients who consult with GPs and practice nurses exposed to training in BCC. These will be compared to outcomes for patients consulting in practices where GPs and practice nurses have not been exposed to training in BCC.

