### Study Intervention

The *intervention *group will receive the blended BCC Training Programme; the *control *group will provide usual care with the offer of training after the study period. This course will move through clinician engagement, preparation, practice and maintenance, in which e-learning will be blended with face-to-face training, and ongoing support provided by MI trained facilitators. A pilot with two practices was used to construct the cases for the video-rich e-learning programme.

The intervention will be called the *Talking Lifestyle *learning programme, which takes practitioners through a portfolio-driven set of learning activities. Its goal is not to ensure complete clinical competence in the use of a guiding style for talking about behaviour change, but rather to start this process. As such it is an introduction to a set of skills that learners can practice and improve as they refine their efforts in everyday practice.

The programme derives much of its content from MI, but also integrates experience from other sources, like behaviour therapy. In developing the intervention the goal was to adapt these more complex psychological methods into a form that is applicable in the everyday practice of doctors and nurses in primary care. The intervention seeks to engage practitioners in thinking about the value of a more flexible shifting between communication styles with patients and to consider the more refined use of a guiding style when talking about behaviour change [24]. Of potential significance is the decision taken for practical reasons not to train clinicians in listening skills, which lie at the heart of motivational interviewing, but to focus on the more general adoption of a guiding style characteristic of BCC.

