### Protecting against bias

Practices who volunteer for the study are likely to be motivated to have access to the intervention, so those who are allocated to the control group may be disappointed. In order to avoid differential dropout between the experimental and control groups, we will offer those practices in the control group the opportunity to complete the training programme after the one year study period. Careful characterisation of the participating practices, clinicians and patients will be undertaken to judge the external validity of the study findings.

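### Randomised practices that know their arm may invite patients to the one-year visit and take its secondary measurements, with no bar on the participating GP or nurse

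*Protocol article*

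**What the plan says.** Three statements in the Follow-up section of the protocol article give practices a part in follow-up.

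- Invitations to the one-year visit: "patients will be invited, either by the research team or the participating practices directly, to attend a follow-up appointment at their practice".
- Measurement: "The researchers and practice staff (if appropriate) will be fully trained in the use of the devices for measuring cholesterol/HDL, cotinine and blood pressure".
- General responsibility: "The study team and the participating practices (if appropriate) will be responsible for research-related follow up".

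The Study Design section fixes the unit of allocation: "This study is a cluster randomised controlled trial with randomisation at the level of practice". The abstract states that one GP and one nurse take part per practice, and adds: "In intervention practices both clinicians will receive training". Under Study Intervention, the control "group will provide usual care with the offer of training after the study period".

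The Secondary Objectives list cholesterol/HDL, cotinine in reported quitters, waist-to-hip ratio and blood pressure at one year. The Outcome Measures section adds body mass index at the same follow-up.

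**The concern.** The participating clinicians cannot be kept unaware of the allocation, because they either receive the training or do not. In such a trial, protection of measured outcomes depends largely on who measures and on who brings patients back. The text leaves both tasks open to the practices being compared.

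Two routes to bias follow. First, a measurer who knows the arm, and may have a stake in it, can affect a blood pressure reading or the placing of a tape for waist and hip, without any intent to do so. Second, a practice that issues its own invitations can, by its effort or its choice of whom to press, change which patients attend. If that differs by arm, the patients measured are no longer comparable, and this reaches all the visit measures, including those a device reads objectively. What is at stake is the credibility of the physical and biochemical secondary outcomes, the results a reader would look to for support of the self-reported changes.

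**Working it through.** No figure in the article bears on this point, so the check is a comparison of the text.

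1. **Do the assessors know the allocation?** Practices are randomised (Study Design). In intervention practices both participating clinicians are trained (abstract), and control practices give usual care with training offered later (Study Intervention). Both participating clinicians therefore know their arm. Other practice staff may know it too.

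2. **May practices act at the one-year visit?** Yes. The Follow-up section names them as possible senders of the invitation and their staff as possible users of the measuring devices. Both roles are optional, so the text permits them without requiring them.

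3. **Are the participating GP and nurse excluded?** No. The text speaks of practice staff without restriction. The only mention of blinding is in the Randomisation section and concerns passing candidate allocations to an independent statistician. The section on protecting against bias deals with differential dropout of practices and with external validity, not with outcome assessment.

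4. **Which outcomes are exposed to the measurer?** Blood pressure is named in the device-training sentence. Waist-to-hip ratio is not, but the Outcome Measures section places it at the same one-year follow-up. Both depend on how the measurement is taken. Cholesterol/HDL by finger-prick test and cotinine by a dedicated device leave little room for the measurer.

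5. **Which outcomes are exposed to differential attendance?** All measures taken at the visit, since each is available only for those who come. The 12-month behavioural questionnaire is sent separately, before the visit invitation, so it does not depend on attendance.

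6. **Does the analysis remove the problem?** No. The multilevel models in the Main Analysis section allow for correlation within practices. They do not correct a shift in measurement or in attendance that runs along the randomised arm.

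7. **Is the primary outcome involved?** It is patient self-report at three months (Primary Objective), gathered by a questionnaire sent to the patient, with non-responders telephoned and "invited to either return the questionnaire by post or to complete it over the phone". The text names no caller and gives practices no stated part in this step.

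**The case against.** The strongest reply is that the practice role is conditional, that the key measurements use devices, and that a journal article leaves staffing detail to the full protocol. Part of this stands. The role is optional, and the text does not say that the trained nurse will measure; that is only a possibility it leaves open. The article also says that results are fed back to clinicians, which may suggest that someone else was expected to take them. Device readings of cholesterol/HDL and cotinine offer little scope for the measurer. But the point does not rest on silence. The article expressly admits practice staff to both tasks and attaches no limit.

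Three stronger readings are tempting and should not be drawn.

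- *That practices collect the primary outcome by telephone.* The sentence on responsibility for follow-up is broad, but the three-month step mentions no practice involvement. A bias in the primary result could be put in numbers only by inventing both the share of telephone completions and the shift per call.
- *That who does each task varies with local availability and resources.* That phrase governs where appointments are held, not who carries them out.
- *That the article concedes biased measurement.* The statement "Practices who volunteer for the study are likely to be motivated to have access to the intervention" introduces a remedy for dropout among disappointed control practices. It shows that practices are not indifferent to allocation, and no more than that.

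**Conclusion.** The point holds for the one-year secondary outcomes. As written, the plan permits staff of the randomised practices, including the two clinicians who know the allocation, to invite patients and to take the measurements. Blood pressure and waist-to-hip ratio are open to influence by the measurer, and all visit measures are open to differential attendance.

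No size can be given: the article does not say how often practices would take on either task, and nothing in it quantifies a resulting shift. The conclusion assumes only that some practices would use the permission. A reader might infer that the trial's main result is compromised. The documents do not support that, because they do not show practices collecting the three-month questionnaire. The change is worth making because the exposure is avoidable at little cost, not because harm has been demonstrated.

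**What to change.** Amend the Follow-up section as follows.

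- Have the research team send all 12-month visit invitations. It is already one of the two permitted senders, and a 12-month questionnaire goes to the same patients shortly beforehand.
- Bar the participating GP and nurse from taking one-year measurements in their own practice. Use the researchers who are already to be trained on the devices or, where that is not possible, practice staff who are not taking part in the trial.
- Record who took the measurements for each patient, and run a sensitivity analysis of the one-year measures by assessor type. Assessor type is not randomised, so this analysis is a check and not a correction.

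The article does not say whether the researchers know the arm. The change removes the assessors with a direct stake but does not by itself make the assessment blind.

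The cost is a reallocation of tasks, one extra field on the visit form, and somewhat less flexibility in scheduling the one-year visits.

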### Analysis

#### Main Analysis

The primary outcome is a composite measure of positive change across four domains. The main analysis will be by intention to treat and will compare the two groups on the proportion of patients reporting positive change in behaviour at three months. This analysis will use a three level (four level if the practitioner level is found to be significant) logistic regression model (fitted using MLwiN v 2.02) to account for clustering at the practice, practitioner and patient level. Sensitivity analysis will be undertaken including alternative methods to allow for non-response.

Secondary outcomes of intentions and actual reported change in each individual behaviour (smoking, drinking, eating and exercise), validated change in smoking and BMI will be assessed using similar three-level (or four-level) regression models. Levels of patient enablement and satisfaction post consultation will be compared using multi level linear regression. Scores for general health will be compared between the two groups using multi level linear regression, allowing for repeated measurement at 3 months and one year and controlling for baseline levels. The two groups will be compared on the level of re-consultation with the practice and for certain prescription items (see 'Follow-up') in the 12 months after the index consultation, and the association between contact with trained practitioners and positive behaviour change will be assessed. Furthermore, the degree to which the participating patients feel capable of effectively managing their health at 12 months after the index consultation will be examined.

### Process Evaluation

The process evaluation will allow us to explore the impact of different aspects of the intervention, and particular barriers or facilitators towards implementation of the intervention [74]. We will:

1. Examine participation in the seminars and use of software supported learning. We will map the clinicians' use of the system (how often they log in, which pages they use) in relation to the primary outcome.

2. Complete qualitative interviews with around 15 clinicians in the control group to explore their views regarding practical aspects of taking part in the study and also the impact of the screening process on their practice. Around 15 clinicians in the experimental group will also be asked about these issues; however, these interviews will also explore ongoing use of the website, the communication skills, and the acceptability and perceived usefulness of various components of the intervention. The interviews will be conducted over the telephone and they will be audio recorded. They will last approximately 20-40 minutes. The items on the interview schedule and the analysis for the experimental group will be guided by the work of Richard Grol on issues to be considered when trying to change clinical practice [75].

3. Examine data from the simulated consultations to explore the intervention clinicians' competence in BCC using the Behaviour Change Counselling Index (BECCI) [76].

If the trial does not show an effect, the process evaluation will be useful in exploring possible reasons for this.

#### Qualitative Analysis

We will employ standard thematic analysis techniques, where transcripts will be closely examined to identify themes and categories [77]. Codes will be applied to these broad themes which will then be broken down further into sub-codes. Agreement on concepts and coding will be sought between members of the research team in order to ensure reliability. A proportion of the data (30%) will be coded by two different team members to check on reliability of the coding scheme. The interviewing will be iterative; where new themes emerge we will incorporate them into the interviews. Interviews will continue until all the themes are saturated, previous experience suggests that this will be around 30 interviews [78,45,79]. Thematic analysis will be supported by the use of computer assisted qualitative analysis software (NVIVO).

### Health Economics

As the intervention may have different impacts on each of the four studied behaviours, the economics of Pre-Empt will take the form of a costs - consequences analysis where costs will be assessed against the full range of outcomes. While such analysis cannot produce definitive conclusions regarding cost effectiveness, it will identify the costs of achieving any effects. Costs of the intervention will include the cost of training, potentially longer consultations in intervention practices, subsequent re-consultations and use of relevant NHS resources such as prescribed drugs (e.g. orlistat for weight loss) and specialist services (e.g. smoking cessation clinics). Duration of consultation will be estimated using clinical software. All other resource use will be monitored prospectively. Training costs will include trainer and learner time - including time online - as well as materials, travel, etc. Since education represents a one-off cost which may produce a stream of benefits over time, the costs of training will be annuitized over an (initial) presumed life of 5 years. Resources will be valued using standard methods [80] and mean differential costs between groups will be estimated.

To account for clustering effects, a two-level model will be used to estimate mean total costs for intervention and control groups [81]. Given the nature of the study design and the elements that make up the cost variable, it is unlikely that the data would be highly positively skewed. However, in the case of significant departure from normality, a generalised linear mixed model, which allows for random centre or practice effects but accommodates positively skewed data, will be used [82]. Multiple regression models for cost data will be estimated using MLwiN v2.02 and STATA v10 software.

## Discussion

This trial will be the first to evaluate the effectiveness of training primary care health professionals in BCC in a primary care setting using a novel blended learning training programme. The goal is to engage practitioners so that they use BCC in their health behaviour consultations in every day primary care. Opportunistic engagement by health professionals potentially represents one of the most cost effective medical interventions. This study integrates an existing training model and method into a blended learning programme and support service to enable practitioners to routinely use BCC by providing them with new tools to encourage and support people to make healthier choices.

The findings of this study will advance current knowledge within the field of patient and clinician behaviour change as well as the way educational interventions can efficiently and effectively be delivered, and inform future research. Patients who receive this intervention have the potential for improved long term health as well as improved communication with their nurse or GP; patients are seen as active problem solvers and drivers of their own behaviour change plans.

If the study shows the intervention is effective, then the training programme could be disseminated across the NHS so that all primary care practitioners can gain skills in talking to people about changing health related behaviour and the broader public will have greater opportunity to benefit from this intervention. This could improve the health of the population and in the long-term lead to a reduction in the cost of treating chronic diseases associated with risky behaviours. However, if the study shows no effect, then the research focus needs re-considering and/or the intervention examined for potential modifications.

### Protecting against bias

Practices who volunteer for the study are likely to be motivated to have access to the intervention, so those who are allocated to the control group may be disappointed. In order to avoid differential dropout between the experimental and control groups, we will offer those practices in the control group the opportunity to complete the training programme after the one year study period. Careful characterisation of the participating practices, clinicians and patients will be undertaken to judge the external validity of the study findings.
